### Adverse events

Adverse events are assessed and judged twice a year by an independent committee. More than half of the votes should be matched to finalize the decision. Adverse events are listed in Table 2. Any unexpected medical events or laboratory findings are also defined as adverse events. Atrial arrhythmia alone is not classified as an adverse event. Instead, it is considered as the primary and/or secondary outcome.

**Table 2 pone.0280359.t002:** Adverse event and safety outcome.

Adverse event • Death caused by •The cardiovascular event •Other causes related to therapy and underlying disease(s) • Life-threatening events related to the cardiovascular cause, therapy, or underlying disease(s) determined based on clinical decision • Any unexpected medical events or laboratory findings Safety outcome • Genitourinary infection* • Renal dysfunction** • Symptoms of volume depletion • Diabetic ketoacidosis • Hypoglycemia • Fracture • Lower limb amputation

* Symptomatic genitourinary infection as at least one event.

** Deterioration of renal function, change in the Chronic Kidney Disease stage (KDIGO 2021) [29].

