The rhythm control strategy for AF will be followed, independent of the type of hypoglycemic agents received. This strategy includes two sessions (Fig 2). In session 1, an AAD will be assigned to every participant and taken for at least 3 months. If patients have persistent AF, cardioversion will be performed with AAD. During the follow-up, those with recurrent AF should step up to session 2, which involves treatment with radiofrequency ablation (RFA) or CRYO-balloon ablation (4 pulmonary vein isolation; 4PVI). For participants of session 2, the follow-up will begin with the moment RFA or cryotherapy is applied, which will be regarded as 0-month; follow-up will be conducted every 3 months for the next 12 months. The rhythm control strategy will be conducted as per the clinical guidelines of 2020 ESC [30] and 2019 AHA/ACC/HRS guidelines [20] for AF.

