### Treatment: DM control (allocation)

The subjects will receive oral hypoglycemic agents for glucose control; the type of agents will be determined by randomization. Patients using SGLT-2 inhibitors to control their serum glucose will be specified as the case group, while those using other hypoglycemic agents (e.g., metformin, meglitinides, sulfonylureas, DPP-4 inhibitors, GLP-1 receptor agonists, α-glucosidase inhibitors, and thiazolidinediones) to control their serum glucose will be classified as the control group. The number, type, and dosage of the agents will be individualized at the discretion of the physician in accordance with the 2021 ADA guidelines [31], considering factors such as the kidney function, age, and cardiovascular status.

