### Study status and organization

Ewha Womans University Mokdong Hospital is responsible for this trial, and the Institutional Review Board (IRB) of Ewha Womans University Mokdong Hospital approved this research plan, including the written consent form (S2, S3 and S4 File). In addition to Ewha Womans University Mokdong Hospital, at least seven other tertiary hospitals in South Korea are now preparing for IRB approval of each hospital with the same research plan.

This study complied with the fundamental spirit of the clinical trial management standards of the Helsinki Declaration (revised 2013) and the International Conference on Harmonisation of Technical Requirements for Registration of Pharmaceuticals for Human Use–Guidelines for Good Clinical Practice (ICH-GCP). The study was initiated after approval of the IRB in each medical center, and after approval, centers recruited patients and the therapies were administered following the appropriate study protocol and clinical standards.

Patients who met the inclusion criteria and voluntarily agreed to enroll in the study provided written informed consent, which was reviewed and approved by the IRB of each participating hospital after sufficient explanation about the research process. Personal identifiers were kept confidential by the researcher, and the research data was recorded with initials and research subject identification information was coded.

All adverse events reported by the subjects during a 3-month follow-up were reported at meetings between researchers four times a year and evaluated by an independent committee. Interruption of participation was decided when the above adverse reaction was a considerable side effect of the SGLT-2 inhibitors (dapagliflozin and empagliflozin), as informed by the Ministry of Food and Drug Safety, or was a serious adverse event unrelated to causality.

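### The adverse-event catch-all is limited to unexpected events, so expected, non-life-threatening harms outside seven named safety outcomes have no category

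*Protocol article*

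**What the plan says.** The Adverse events section refers to Table 2 for the list of adverse events and adds: "Any unexpected medical events or laboratory findings are also defined as adverse events". Table 2 carries the same catch-all with the same adjective. Neither place defines it. Table 2 has two other adverse-event categories:

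- deaths from a cardiovascular event, or from other causes related to therapy and underlying disease;
- "Life-threatening events related to the cardiovascular cause, therapy, or underlying disease(s) determined based on clinical decision".

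Under a separate subheading, Table 2 names seven safety outcomes: symptomatic genitourinary infection, renal dysfunction, volume-depletion symptoms, ketoacidosis, hypoglycemia, fracture and amputation of a lower limb. None is confined to one arm. One exception is explicit: "Atrial arrhythmia alone is not classified as an adverse event".

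On exposure, Study design and participants says: "In session 1, an AAD will be assigned to every participant and taken for at least 3 months". It adds cardioversion for persistent AF and, on recurrence, a second session "which involves treatment with radiofrequency ablation (RFA) or CRYO-balloon ablation". The allocation section gives the control drugs as, for example, "metformin, meglitinides, sulfonylureas, DPP-4 inhibitors, GLP-1 receptor agonists, α-glucosidase inhibitors, and thiazolidinediones". Table 5 schedules an adverse-event history at 3, 6, 9 and 12 months. The abstract and the conclusions both say that safety will be evaluated.

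**The concern.** Whether an event is an adverse event should not depend on whether it was foreseen. Most harms of established drugs and procedures are foreseen, so a rule that admits only unexpected events leaves out the harms most likely to occur, unless another category catches them. Here the other categories are death, threat to life and seven named items. None of the seven is specific to an AAD, to cardioversion or to ablation, although these treatments are part of the trial's own rhythm-control strategy.

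What is at stake is the completeness of the safety data. A site that applies the definition as written would have no place for a recognised, milder procedural complication or AAD side effect. Because the word is undefined, sites could also apply it differently.

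**Working it through.** No figure in the plan depends on this definition, so the check is one of reading. The question is which events fall into at least one category of Table 2.

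**Step 1. Classify typical events under the written rule.**

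| Event | Category that takes it |
|---|---|
| Unexpected laboratory finding, either arm | Catch-all |
| Symptomatic genitourinary infection, either arm | Seven safety outcomes |
| Hypoglycemia on a comparator such as a sulfonylurea | Seven safety outcomes |
| Life-threatening ablation or AAD complication | Life-threatening events related to therapy |
| Recognised, non-life-threatening AAD side effect outside the seven | None |
| Recognised, non-life-threatening cardioversion or ablation complication outside the seven | None |
| Recognised, non-life-threatening side effect of a comparator, or of an SGLT-2 inhibitor, outside the seven | None |

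**Step 2. Look for wording elsewhere that widens the definition.**

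- The follow-up section and Table 5 require an adverse-event history at visits, and the follow-up section also asks about other specific illnesses. They say when to ask, not what counts.
- Study status and organization sends all adverse events reported by subjects to meetings and to the committee. It uses the defined term without enlarging it.
- The same section says: "Interruption of participation was decided when the above adverse reaction was a considerable side effect of the SGLT-2 inhibitors". This governs interruption of participation. It suggests that known side effects were in mind, but it does not define an adverse event.

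Nothing found closes the gap in the last three rows of the table.

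**Step 3. Count the exposed participants.** Inputs from the statistical plan are 716 enrolled, 358 per group, 50% of AAD users stepping up to ablation, and a 40% reduction in AF.

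- AAD: 2 × 358 = 716, all participants.
- Ablation, if 50% applies in both arms: 358 × 0.50 = 179 per arm, ratio 1.0.
- Ablation, if 50% is taken as the control rate and the 40% reduction is carried over in full to step-up: 179 against 179 × 0.60 = 107.4, about 107; ratio 179 / 107.4 = 1.67.

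These are counts of people treated, not of events lost. The documents give no complication or side-effect rate, so the number of uncategorised events cannot be derived from them.

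**The case against.** The strongest reply is that *unexpected* is loose wording for *untoward*. The sentence says that such events are also adverse events, so it is meant to enlarge the list. Atrial arrhythmia is then expressly excluded. Recurrence of AF is about the most expected event in this trial, and an exclusion would hardly be needed if expected events were already outside the rule. The article also claims compliance with ICH-GCP. This may well be the intent, but these are hints. The definition is stated twice with the restrictive word, and nothing replaces it.

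A second reply is that this is a condensed article and that coding rules sit in the full research plan. That would answer a missing detail. It does not answer a definition that the article itself states and repeats.

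Three stronger readings are tempting, and the documents do not support them:

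- **That known SGLT-2 harms are counted and comparator harms are not.** The seven outcomes apply to both arms and include hypoglycemia, renal dysfunction and fracture. Only harms outside the seven are lost, in either arm.
- **That the interruption rule contradicts the definition.** It serves another purpose and is compatible with Table 2, which lists several safety outcomes of its own.
- **That the loss is tilted about 1.7 to 1 against one arm.** The statistical plan gives 50% for AAD users without naming an arm. The follow-up section makes ablation depend on symptoms and physician discretion as well as recurrence. The ratio of 1.67 needs an arm-specific step-up rate that the plan does not state; with equal step-up it is 1.0.

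It would also go too far to say that these events are never seen. History is taken at every visit, and life-threatening therapy-related events are counted. What lacks a place is the classification of the milder, expected ones.

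**Conclusion.** The point holds as a defect of wording. Read literally, the adverse-event definition and Table 2 leave expected, non-life-threatening events outside the seven safety outcomes without a category. All participants are exposed through the AAD, and some through cardioversion or ablation.

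The consequence is mainly under-capture in both arms. The comparison between arms would be distorted only if use of these treatments, or the rate of unlisted drug harms, differs by arm. The documents neither state nor exclude that. The size cannot be given from the documents, and the efficacy analysis, sample size and power are untouched. The conclusion assumes that sites apply the text as written; if they read it as *untoward*, the practical loss is small. The change is worth making because it is cheap and makes the safety comparison more complete.

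**What to change.** In the Adverse events section and in Table 2, replace the catch-all with: *any untoward medical event or laboratory finding, whether expected or not and whether or not related to study drug, AAD, cardioversion or ablation*. Keep the stated exception for atrial arrhythmia alone. Record expectedness as an attribute of each event, not as a condition for counting it. Compare all adverse events by randomised group, beside the seven safety outcomes.

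The cost is a wording change in two places and some extra coding and committee listing. No visit is added, since adverse-event history is already scheduled at all four follow-up visits.

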### Statistical plan, sample size, and power determination

In this study, 716 patients will be enrolled from 7 tertiary medical centers. The sample size was determined based on the primary outcome, i.e., the SGLT-2 inhibitors should show 40% reduction in AF after a year of treatment [32] and 50% of AAD users should step up to the ablation therapy [33,34]. Assuming 10% follow-up loss, the sample size of 716 patients (358 in each group) is expected to achieve 80% power and an alpha-level of 5% to detect the difference. The study is powered to demonstrate the superior additive effect of SGLT-2 inhibitors over other hypoglycemic agents using the Chi square method. AF recurrence rate and ratio of sinus rhythm on 24-h holter EKG will be analyzed using Chi square test, and left atrial size, NT-pro BNP and quality of life (AFEQT) score on 12-month final follow-up will be analyzed by student t-test. Disease-free survival and overall survival during the follow-up period will be calculated using Kaplan-Meier method. Mono-variable and multi-variable cox regression analysis will be used to calculate hazard ratio of SGLT-2 group.

To reduce the selection bias, all subjects will be randomized to allocate the hypoglycemic agents according to random number table. Missing data is planned to be controlled using multiple imputation.

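### Table 2 defines its death and life-threatening lines by relatedness, so arm counts on those two lines depend on attribution in an open-label trial

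*Protocol article*

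**What the plan says.** The Adverse events section and its Table 2 set out three adverse-event lines, followed by a separate list of seven safety outcomes.

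- **Death** has two entries: death from a cardiovascular event, and "Other causes related to therapy and underlying disease(s".
- **Life-threatening events** are given as "Life-threatening events related to the cardiovascular cause, therapy, or underlying disease(s) determined based on clinical decision".
- **The general line** carries no relatedness condition, and the text repeats it: "Any unexpected medical events or laboratory findings are also defined as adverse events".

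On who judges, the same section states: "Adverse events are assessed and judged twice a year by an independent committee". A majority vote settles each decision. The Study design section describes open treatment with blinded endpoint assessment.

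Two other places bear on the point. The statistical plan says "Disease-free survival and overall survival during the follow-up period will be calculated using Kaplan-Meier method". The Study status and organization section, in its rule on interrupting participation, includes the case where the event "or was a serious adverse event unrelated to causality".

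**The concern.** The Abstract and the Conclusions both say that the trial will evaluate safety. Deaths from any cause and all life-threatening events are the safety counts least open to judgement, because whether they happened is rarely in dispute. Table 2 makes both lines conditional on a relatedness judgement, and for life-threatening events it refers that judgement to clinical decision.

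Where treatment is open and the assessor's blinding is not stated, attribution can differ between arms even if the underlying event rates do not. A comparison read off these two lines would then mix the treatment effect with differences in attribution.

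**Working it through.** The article gives no figure on this point, so there is none to reproduce. The check is to follow a serious event through the table wording.

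**Step 1: where each event lands under Table 2.**

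| Event | Judged related | Judged unrelated, but unexpected | Judged unrelated and not unexpected |
|---|---|---|---|
| Death | Death line | General unexpected-event line | No adverse-event line |
| Life-threatening event | Life-threatening line | General unexpected-event line | No adverse-event line |

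The middle column is the usual fate of an unrelated serious event. The event stays in the adverse-event data, but on a line that pools it with any unexpected finding, laboratory findings included. The last column is a narrow gap, whose width depends on how *unexpected* is applied; the article does not define the term.

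**Step 2: what else counts the same events.** Overall survival, read in its usual sense, counts every death whatever its cause, so the death row has a second source. It is only partial cover: overall survival is named in the statistical plan but is not among the outcomes in Table 1 or Table 2. Nothing comparable exists for the life-threatening row. The seven safety outcomes carry no relatedness condition, but they are specific diagnoses and do not add up to all life-threatening events.

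**Step 3: what the condition does to an arm comparison.** Let D be the true number of events in an arm and r the share judged related. The line shows D × r. The ratio between arms on that line is therefore

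(D in SGLT-2 arm ÷ D in control arm) × (r in SGLT-2 arm ÷ r in control arm).

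If r is equal in the two arms, the ratio is undistorted on average and only events are lost. If r differs, the ratio is multiplied by the ratio of attribution shares. With every event counted, r = 1 in both arms and the second factor disappears. The article gives no value for D or r, so the second factor cannot be sized, nor its direction fixed.

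**Step 4: who sets r.** Committee adjudication is stated, but whether the committee knows the arm when it judges adverse events is neither stated nor excluded. The clause on clinical decision names no decision-maker. Elsewhere in the Discussion, clinical decisions are those of the treating physician, who knows the arm. That makes a clinician's judgement one possible reading here, but does not establish it.

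**The case against.** The strongest reply is that little is lost. The general line catches most unrelated events, overall survival supplies an all-cause count of deaths, an independent committee votes on adverse events, and *underlying disease* is broad enough in patients with AF and DM that few deaths would fall outside it. The statistical plan names no between-arm test of the Table 2 lines. Full definitions and committee procedures may also sit in a longer protocol that is not shown.

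Most of this stands, and it rules out several stronger readings that a reader might infer:

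- **That serious events leave the safety data altogether.** The general line contradicts this, apart from the narrow gap in the last column of the table.
- **That relatedness is known to be judged with knowledge of the arm, before the committee sees the case.** No text says so. The clause on clinical decision can also be read as qualifying what counts as life-threatening.
- **That the Study status section contradicts Table 2.** Its wording on causality governs interruption of participation, not how events are tabulated.
- **That a false excess of a given size would appear.** Any such figure would need assumed mortality and attribution rates, and even its direction is unsupported: both arms are open and take active glucose-lowering drugs under the same rhythm-control strategy.

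What the reply does not remove is the wording itself. The relatedness condition is stated in Table 2, so it is not detail merely left out of a condensed article. Moving an unrelated life-threatening event to a mixed line still takes it out of the count that a reader would look up.

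**Conclusion.** The point holds in a limited form. Two of the three adverse-event lines in Table 2 are defined by relatedness, so their arm counts depend on attribution. For deaths the weakness is partly offset by overall survival, provided that term has its usual all-cause meaning. For life-threatening events no all-cause line exists.

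The conclusion assumes that the arms will be compared on Table 2 events, which is the natural reading of a randomized trial with a stated safety aim although no test is named. It does not assume that the committee is unblinded; it rests on blinding for adverse events not being stated. No numerical size is claimed. This is a modest defect of definition, not evidence that serious events will be lost.

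**What to change.** Reword the two lines of Table 2 as *Death from any cause* and *Any life-threatening event, whatever its cause*, and compare the arms on these counts. Remove the reference to clinical decision as a condition for counting. Record cardiovascular or therapy-related status afterwards, as a sub-classification made by the existing independent committee with the arm masked in the case material, and state that masking in the Adverse events section.

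The cost is small. Adverse-event history is already scheduled at the 3-, 6-, 9- and 12-month visits in Table 5, and the committee already exists. It would classify a few more events, and someone would have to remove the arm from the files it reads. No treatment rule changes.

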### Study design and participants

This is a multicenter study with a prospective, open, blinded endpoint design (Fig 1). It is a 1:1 randomized and controlled study that compares the rhythm control effect of SGLT-2 inhibitor therapy to other oral hypoglycemic agents in patients with AF and DM (Fig 2).

**Fig 1 pone.0280359.g001:**
[figure not shown]
Completed SPIRIT schedule of trial. The rough schedule of BEYOND trial is summarized in a table. If AF is recurred during the follow-up period, patient will get a catheter or CRYO-balloon ablation and have an additional one-year follow-up period after ablation.

**Fig 2 pone.0280359.g002:**
[figure not shown]
Flow chart of the trial. Brief flow of the BEYOND trial described as a schematic diagram. Patients who enroll this trial will be randomly administrated SGLT-2 inhibitor or other DM medication while applying stepwise rhythm control strategy for AF.

Patients diagnosed with AF within a year, who have never undergone any ablation treatment, newly diagnosed with DM, and with ages between 18 and 80 years will be selected as the study participants. They will be enrolled in 7 tertiary medical centers from the Division of Cardiology and the Division of Endocrinology. As patients diagnosed with AF also tend to check for DM to calculate the CHAD2-VASc score, those who have been diagnosed as AF in the prior year and newly diagnosed with DM in the follow-up can be recruited for the trial in the Division of Cardiology. To identify patients for enrollment in the Division of Endocrinology, every patient newly diagnosed with DM during the enrollment period will be asked for 12-lead ECG and 24-h Holter ECG; those with AF > 10 s in 12-lead ECG or >30 s in 24-h Holter ECG can be recruited for the trial. All participants must meet the required inclusion (Table 3) and exclusion criteria (Table 4) at the point of randomization. The participants should otherwise be healthy and use only oral hypoglycemic agents, not subcutaneous agents, for glycemic control.

**Table 3 pone.0280359.t003:** Inclusion criteria.

• At least one episode of AF* that is documented during the prior year by any kind of ECG recording. • Type 2 DM was diagnosed (HbA1c > 6.5%) and the patient was using oral hypoglycemic agents only for glycemic control. • At least 18 years old, but not older than 80 years. • Normal ECG parameters, measured in sinus rhythm (QRS width ≤ 120 ms, QTc interval < 440 ms, and PQ interval ≤ 210 ms in a 12-lead ECG). • Be able and willing to give informed consent.

*AF episode must last longer than 30 s on single ECG, 10 s on 12-lead ECG or 24-h Holter ECG.

AF, atrial fibrillation; DM, diabetes mellitus; ECG, electrocardiogram.

**Table 4 pone.0280359.t004:** Exclusion criteria.

• Any disease that limits life expectancy to under 1 year • Subject for another clinical trial within the past 2 months • Under 18 years old or over 80 years • Pregnant women • Lactating women • Drug abuser • Type 2 DM treated by recombinant insulin • Diagnosis of Type 1 DM, MODY, or secondary DM • HbA1c ≥ 12% or HbA1c < 6.5% at diagnosis • Previous treatment with any SGLT-2 inhibitor • Renal dysfunction (eGFR-CKD-EPI < 30 mL/min/1.73 m^2^) • Chronic cystitis and/or recurrent genitourinary tract infections (3 or more in the last year) • Unexplained hematuria at baseline study • Systolic BP > 180 mmHg or diastolic BP > 100 mmHg at baseline study • Systolic BP < 95 mmHg at baseline study • Previous treatment with AF ablation • Acute cardiovascular event [e.g., stroke, acute coronary syndrome (ACS), revascularization, decompensated HF, sustained ventricular tachycardia, return of spontaneous circulation (ROSC)] <8 weeks prior to baseline study • Severe valvular disease or have prosthetic valve • Treatment with chronic oral steroid (>30 consecutive days) at a dose equivalent to oral prednisolone ≥ 10 mg/d, within the past 1 month • History of any malignancy within 5 years • Clinically profound hepatic dysfunction • Clinically uncontrolled thyroid dysfunction • Patients incapable of completing the trial because of any severe medical condition by clinical decision • Patients with poor compliance (defined as 80–120%), except for reasonable situations judged by physician

DM, diabetes mellitus; MODY, maturity onset diabetes of the young; EPI, epidemiology collaboration; BP, blood pressure; AF, atrial fibrillation; HF, heart failure.

The rhythm control strategy for AF will be followed, independent of the type of hypoglycemic agents received. This strategy includes two sessions (Fig 2). In session 1, an AAD will be assigned to every participant and taken for at least 3 months. If patients have persistent AF, cardioversion will be performed with AAD. During the follow-up, those with recurrent AF should step up to session 2, which involves treatment with radiofrequency ablation (RFA) or CRYO-balloon ablation (4 pulmonary vein isolation; 4PVI). For participants of session 2, the follow-up will begin with the moment RFA or cryotherapy is applied, which will be regarded as 0-month; follow-up will be conducted every 3 months for the next 12 months. The rhythm control strategy will be conducted as per the clinical guidelines of 2020 ESC [30] and 2019 AHA/ACC/HRS guidelines [20] for AF.

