## Abstract

SGLT-2 inhibitor, traditionally used for glycemic control, has several beneficial effects that can help manage heart failure (HF). SGLT-2 inhibitors reduce the risk of cardiovascular mortality in patients with HF. As atrial fibrillation (AF) is closely associated with HF and diabetes mellitus (DM) is a risk factor for AF, we assume that SGLT-2 inhibitors will also show therapeutic benefits regarding AF, especially for rhythm control. This trial has a multicenter, prospective, open, blinded endpoint design. It is a 1:1 randomized and controlled study. A total of 716 patients who are newly diagnosed of AF and DM within 1 year will be enrolled from 7 tertiary medical centers. The trial is designed to compare the effects of SGLT-2 inhibitors and other oral hypoglycemic agents on atrial rhythm control in patients with AF and DM. The primary outcome is the recurrence of AF within a year (including post-antiarrhythmic drugs (AAD) or ablation). The secondary outcomes are the ablation rate within a year, change in AF burden, size of the left atrium, NT-proBNP, the AF symptom score, and the quality of life. This trial will prospectively evaluate the effect and safety of SGLT-2 inhibitors on AF rhythm control in patients with DM. It will provide an invaluable dataset on rhythm control in AF with DM for future studies and offer novel information to assist in clinical decisions. (BEYOND trial, ClinicalTrials.gov number: NCT05029115. https://clinicaltrials.gov/ct2/show/NCT05029115).

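### The eligibility tables admit stable heart failure with reduced ejection fraction, an undefined health phrase may exclude it, and such a patient can be allocated to the non-SGLT-2 arm

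*Protocol article*

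**What the plan says.** Under Study design and participants, the Protocol article states: "All participants must meet the required inclusion (Table 3) and exclusion criteria (Table 4) at the point of randomization". The next sentence adds: "The participants should otherwise be healthy and use only oral hypoglycemic agents". The oral-agents half of that sentence is repeated as a criterion in Table 3. The health half has no counterpart in either table.

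Table 4 mentions HF once, in a list of acute cardiovascular events that ends "decompensated HF, sustained ventricular tachycardia, return of spontaneous circulation (ROSC)] <8 weeks prior to baseline study". Neither table sets a limit on chronic HF, LVEF or NYHA class, although both LVEF and NYHA are recorded (Follow-up and detection of AF recurrence). Table 4 also has a clinical-decision exclusion: "Patients incapable of completing the trial because of any severe medical condition by clinical decision".

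On treatment, the section Treatment: DM control (allocation) says "the type of agents will be determined by randomization". Patients using the other listed classes "to control their serum glucose will be classified as the control group". Within that, the physician chooses the number, type and dose of agents, "considering factors such as the kidney function, age, and cardiovascular status".

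On the evidence, the Abstract states: "SGLT-2 inhibitors reduce the risk of cardiovascular mortality in patients with HF". The Discussion repeats the mortality benefit. The Introduction reports that two drugs of the class reduce cardiovascular death or worsening HF whether or not the patient has diabetes. One of the two trials it cites is named for reduced ejection fraction.

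**The concern.** The mandatory tables and the sentence beside them can give opposite answers for the same patient. Take someone with stable chronic HF and reduced ejection fraction, newly diagnosed diabetes, AF within the year, no previous SGLT-2 inhibitor, and ECG and blood pressure within the limits. The tables admit this patient. The general-health phrase, read strictly, does not.

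Two things are at stake. The first is safety: a centre that follows the tables may allocate this patient to a regimen defined by other drug classes, when the article's own rationale is that the withheld class lowers cardiovascular death in HF. The second is consistency: seven centres are to share one plan, and eligibility for this group would depend on how each of them reads a phrase.

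Such patients are foreseeable. The Introduction describes AF and congestive HF as common, closely linked and sharing diabetes as a risk factor, and recruitment is from tertiary cardiology and endocrinology divisions.

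**Working it through.** This is a reading of eligibility rules, so the article has no figure to reproduce. The steps below take the patient described above through each rule that could exclude the patient or change the allocation.

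1. **Acute-event exclusion (Table 4).** It applies only if decompensation occurred less than 8 weeks before baseline. A stable patient passes.
2. **Clinical-decision exclusion (Table 4).** It covers patients who cannot complete the trial. A stable HF patient can complete it.
3. **Other filters.** A life expectancy under 1 year, systolic pressure below 95 mmHg, severe valve disease, and the QRS, QTc and PQ limits in Table 3 remove some HF patients. They do not remove stable reduced-ejection-fraction HF as such. The bar on previous SGLT-2 inhibitor use keeps out patients already on the class, and leaves those not yet given it.
4. **Physician discretion (Treatment: DM control).** Cardiovascular status may guide the choice of agent, but the class is set by randomisation. No exception for HF is stated.
5. **Withdrawal rules (Follow-up and detection of AF recurrence; Study status and organization).** These act only after an adverse event.
6. **The general-health phrase.** It is the only text that could exclude the patient, and it is undefined. If it did exclude chronic HF, the HF entry in the 8-week rule would have little left to do. That favours the tables' reading but does not settle the matter.

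Duration: the visit schedule in Table 5 runs for 12 months. Follow-up continues for a further year after ablation, but the article does not say whether the allocated regimen does, so only the 12 months are counted.

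Size: the article gives no share of participants with HF, so the effect is expressed per 1%, with s as the unknown share.

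- Control patients affected: 358 × s. For s = 1%, 358 × 0.01 = 3.58, about 3.6.
- Exposure over the 12-month schedule: 3.58 × 1 year, about 3.6 patient-years.
- Extra otherwise eligible patients needed if they are excluded: 716 / (1 − s) − 716. For s = 1%, 716 / 0.99 = 723.2, and 723.2 − 716 = 7.2, about 7.

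All three go to zero as s does.

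**The case against.** The strongest reply is that the article does contain a limiting condition. In ordinary usage a patient with chronic reduced-ejection-fraction HF is not otherwise healthy, and the 8-week rule may be no more than a washout for acute events, listed as examples, with no implication that chronic HF is acceptable. This stands in part. It shows that the text is ambiguous, and that it would be wrong to say the protocol deliberately enrols these patients. It does not remove the problem, because the criteria declared mandatory at randomisation are the tables, and the tables admit them.

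A second reply concerns the harm. A reader might infer that control patients are barred from SGLT-2 inhibitors and so denied effective HF treatment. The article does not say that. It defines controls by the agents used for glucose control and is silent on use of the class for HF. Rules on concomitant treatment are commonly left to the full protocol, which is not shown. This reply stands: the documents support a possible allocation away from the class, not an established denial of treatment.

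Third, after all the filters the remaining group may be very small, even close to nil. That also stands, and the figure per 1% is a scale, not an estimate.

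Lastly, the Abstract and Discussion speak of HF in general, so limiting an exclusion to reduced ejection fraction is a choice. It is defensible because one of the two cited trials names that group. Allowing the class for HF in the control arm would be another option, but it would weaken the contrast between the arms.

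**Conclusion.** The point holds as a conflict in the eligibility text with a foreseeable safety consequence, and it should be corrected. As printed, Tables 3 and 4 let a stable, SGLT-2-naive patient with reduced-ejection-fraction HF be allocated to the non-SGLT-2 arm for the 12-month schedule, while the article states that the class lowers cardiovascular death in HF. The only text that might prevent this is undefined.

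The number affected is unknown and probably small: about 3.6 control patients per 1% of participants with such HF, on the assumption that the share is the same in both arms of 358. The safety consequence further assumes that the full protocol does not permit controls the class for HF; if it does, the inconsistency between centres remains and the safety concern largely falls away. The article supports neither a claim that many patients would be harmed nor a claim that exposure would exceed the 12-month schedule.

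**What to change.** Make two changes in one amendment.

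1. Add a line to Table 4 that excludes known HF with reduced ejection fraction, or a baseline echocardiographic LVEF at or below a fixed cut-off chosen by the sponsor (40%, for example, which is an assumption here and not a figure from the article). State that the echocardiogram is read before randomisation.
2. Replace the general-health phrase under Study design and participants with a reference to Tables 3 and 4, so that all centres apply one rule. Other stable HF then stays eligible by a clear rule.

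No new test is needed: medical history and echocardiography are already in the baseline column of Table 5, and LVEF is already measured. Table 4 already uses baseline findings (blood pressure, haematuria) for eligibility, so reading a baseline result before allocation is not a new kind of step, though the echocardiogram must be reported in time. The price is slightly slower recruitment, about 7 more otherwise eligible patients per 1% excluded, and a result that does not extend to patients with reduced-ejection-fraction HF.
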